#### Intervention

The experiment will take place over three measurement times on Day 0 (D0), D7 and D21. On D0 subjects will be randomized in 2 groups: experimental and placebo group. Both groups will be assessed on: SPPB, WS, lower limb strength, balance, HRV and cervical spine strength and mobility. They will also be given an SF 36 questionnaire (to complete at home and bring back to D7). Then the experimental group will receive a MFR protocol applied to the cervical spine and the placebo group will receive a placebo light touch protocol. The intervention will be followed by the same measurements as before. This schedule will be reproduced on D7. On D21, only assessment will be done. Measurements will be made by the same experimenter for all sessions for the same patient. The time of presence required is estimated at 4 h maximum: approximately 1h30 on D0 and D7 and 45 min on D21.

The MFR protocol applied to the cervical spine in this study is carried out by one therapist—Osteopath D.O. (Diploma in Osteopathy)- with one year of experience. All the gestures performed and described below are manual osteopathic techniques with myofascial aim, mastered and commonly used in osteopathic practice management. Whatever the patient's allocation group, the techniques are gentle and progressive, the patient's head (lying on his back) remaining in line with the spine.

For the treated group, initially, the manual therapist, seated at the head of the patient, will perform a “suboccipital decompression” [46]—Fig. 2a. To do this, he will position the last 4 fingers of each hand towards the lower part of the occiput, the last phalanges in contact with the sub-occipital muscles. He will look for a so-called “bone contact” on the occiput. He will apply anterior and superior continuous pressure during 15 to 20 chest breaths.

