However, there is no consensus on the frequency or number of treatments necessary with MFR, regardless of the reason for which they are used, for example: chronic low back pain, fibromyalgia, functional capacities… [39, 40]. Whatever the modality of application (massage or osteopathic manual therapy) or location (lower limb or trunk) it seems that only one MFR session have a limited or even non-existent effect on balance [41, 42] while recent studies have shown that two sessions can [43, 44].

To our knowledge, no study has yet proposed to evaluate the effect of a cervical spine MFR protocol on balance in older adults. The main hypothesis of the present study is that a two sessions MFR protocol have a beneficial impact on the balance and motor performance of older adults, which will result in improved balance and WS in the experimental group compared to the placebo group. The study also aims to propose an assessment of the physical parameters of balance, looking for links to validate the contribution of the cervical spine in compensatory mechanisms.

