### Primary and secondary objectives

The primary objective of this work will be to evaluate the influence of some MFR techniques address to cervical spine on WS and SPPB (Short Physical Performance Battery test) score. It can be assessed by the main hypothesis:

H0: SPPB score and WS of MFR protocol group ≤ SPPB score and WS of light touch group.

H1: SPPB score and WS of MFR protocol group > SPPB score and WS of light touch group.

Secondary objectives will be to evaluate the influence of the protocol on other measured balance parameters, including cervical strength and mobility as well as lower limb strength, ground support and HRV. The data can also be used to explore the relationships between the different parameters.

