## Outcomes

### Primary outcome

The primary outcome of this study will be WS and the SPPB test score.

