## Discussion

### Potential impact and significance

This study could not go beyond the recruitment phase in 2019, interrupted by the COVID pandemic, but it is currently envisaged that the protocol will be reinstated in 2022. Indeed, manual therapy has already shown its benefits in the management of pain and its place as the therapy of choice in the "toolbox" of the senior citizen (64). We believe that it is interesting to evaluate its impact on balance with a view to including it in the therapies offered in the context of fall prevention. We hope that the analysis of the results will show, among other things, a significant improvement of the SPPB score and of WS after MFR on D21. We also hope that the analysis of the other parameters: cervical mobility and strength, HRV, plantar support and static posturography will be sensitive to manual therapy and that the results will improve the understanding of the links between the cervical spine and balance parameters.

We recognize that the application of a defined protocol of MFR techniques is a limitation of this study, as this does not represent the current management in manual therapy. Nevertheless, from a scientific point of view, the effects of such a protocol applied to the senior cervical spine must be determined before being combined with other interventions. Other limitations could be cited, such as the lack of long-term follow-up.

As "first-line" practitioners, manual therapists such as chiropractors or osteopaths must be trained in the detection and management of balance disorders in seniors. We believe that this study will provide an innovative and well-argued point of view on the evaluation and integration of the cervical spine in manual treatment protocols in the context of the risk of falls in the elderly, which can be disseminated to manual therapy students and other related professionals so that they may have a new therapeutic option to offer.

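### No primary occasion is named for WS and SPPB, which are measured four times after treatment starts, and no rule says whether both or either must be significant

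*Protocol article*

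**What the plan says.** Under Primary outcome the article states: "The primary outcome of this study will be WS and the SPPB test score". It gives no time point, no change score and no rule for combining the two. The alternative hypothesis, under Primary and secondary objectives, is "H1: SPPB score and WS of MFR protocol group > SPPB score and WS of light touch group", again without an occasion.

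The Intervention section sets the measurement schedule. For D0, after baseline and treatment, and then for D7, it says: "The intervention will be followed by the same measurements as before. This schedule will be reproduced on D7". Finally, "On D21, only assessment will be done".

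The Background frames the main hypothesis as "a two sessions MFR protocol have a beneficial impact on the balance and motor performance of older adults", and notes that a single session seems to have little or no effect on balance.

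The section Statistical analysis and sample size compares the two groups by one-way ANOVA or Kruskal–Wallis at p ≤ 0.05. It has no occasion factor, baseline term or adjustment across outcomes or occasions. The post-hoc tests it lists belong to the group and gender analyses. The only sentence linking the primary outcomes to a day is in the Discussion, which hopes for "a significant improvement of the SPPB score and of WS after MFR on D21".

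**The concern.** A hypothesis about an outcome measured repeatedly is not complete until the occasion is fixed. Here the hypothesis, outcome, test and significance level are all fixed, but the occasion and the both-or-either rule are not. Someone following the text could choose, after seeing the data, which occasion and which outcome decides the trial.

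Two of the available occasions, D0 post and D7 pre, come before the second session. A chance difference minutes after the first session could be presented as confirming H1, although the Background ties the hypothesis to two sessions. At stake are the false-positive rate of the primary claim and whether that claim answers the stated question.

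**Working it through.** **Count of possible comparisons.** From the Intervention section, the occasions after the first treatment are D0 post, D7 pre, D7 post and D21. Two outcomes × four occasions = 8. Only D7 post and D21 follow both sessions: 2 × 2 = 4.

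**What the sample size covers.** Inputs from the sample-size paragraph: difference 0.2 m/s, ±0.2 read as the SD (an assumption), power 90%, alpha 0.05, dropout 10%.

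- Formula: n per group = 2 (z_alpha + z_power)² (SD/difference)².
- One-sided: 2 × (1.645 + 1.282)² × 1 = 17.1, so 18; 18/0.9 = 20. This reproduces the stated 20. The exact t-test also gives 18 (power 90.2%).
- Two-sided: 2 × (1.960 + 1.282)² × 1 = 21.0, so 22; 22/0.9 = 24.4, so 25 (26 by the exact t-test). This does not match.

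So 20 per group fits one one-sided 5% test of WS at one occasion. Sidedness is not stated.

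**False-positive rate by decision rule.** Null trials were simulated with 18 per arm and t-tests, with equal correlation between occasions and a further correlation between outcomes. The documents give no correlations. Those used are assumptions, paired from 0.9 (occasions) with 0.8 (outcomes) to 0.5 with 0.4.

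| Rule | Error rate |
|---|---|
| Any one of eight, two-sided 5% | about 15–28% |
| Any one of eight, one-sided 5% | about 13–25% |
| One outcome, any of four occasions, one-sided 5% | about 9–14% |
| Both outcomes at the same occasion, any of four, one-sided 5%, neither affected | about 3–5% |
| Both outcomes at D21 only | at most 5% |

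- Independence would give 1 − 0.95⁸ = 33.7% for eight tests and 1 − 0.95⁴ = 18.5% for four. These are upper references only. Repeated measures correlate, and WS is taken from the gait part of the SPPB (section WS, SPPB test and plantar support).
- The fourth row depends on the pairing. Over a wider grid (occasions 0.5–0.9, outcomes 0–0.7) it is about 1–6%. A check at 0.5 between occasions with 0.8 between outcomes gave about 8%.
- That row also assumes that neither outcome responds. If one outcome truly responds at every occasion, only the other stands between the trial and a false joint claim, and the error moves towards the third row, about 9–14%.
- The last row needs no simulation. If at least one outcome is unaffected, requiring both to pass at 5% cannot succeed more often than the unaffected one does, which is at most 5%.

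**The case against.** A reader might infer that eight primary tests are planned and that the error rate is therefore 15–28%, or even 34%. The documents do not support that. They say WS and SPPB are measured at these occasions, not that the groups are compared at each, so eight is the most the silence permits. H1 joins the two outcomes with *and*, the sample-size paragraph keeps SPPB as a primary outcome in combination with WS, and the Discussion names both. Taken literally, both must succeed, and with neither affected there is then little or no inflation at the paired correlations. Setting aside the occasions before the second session leaves at most four tests: about 11–17% two-sided if either outcome suffices.

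Nor should the rate of false claims favouring MFR be set against a nominal 2.5%. The hypotheses are directional, and the sample size reproduces only at one-sided 5%.

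It can also be said that this is a condensed article, that Fig. 1 is not shown, that a fuller plan may fix the occasion, and that the Discussion already points to D21.

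These objections limit the size of the problem but do not remove it. No decision rule states the conjunctive reading. Even under it, the free choice of occasion leaves an error of about 9–14% for an unaffected outcome when the other truly responds. The Discussion expresses a hope, not a designation. The occasion is part of the hypothesis that the article itself states, so it is more than detail left to an analysis plan.

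**Conclusion.** The point holds in a conditional form. As written, the article does not determine which result decides the trial, and it lets results after one session stand for a two-session hypothesis. How far the error exceeds 5% depends on a rule the text does not give: from little or nothing (both outcomes required, neither affected), through about 9–14% (one outcome over four occasions, or an unaffected outcome beside one that responds), to about 13–25% one-sided or 15–28% two-sided (any one test suffices). All these ranges rest on 18 evaluable per arm and on assumed correlations. The gap itself, no occasion and no both-or-either rule, rests only on the text.

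**What to change.** Name D21 as the single primary occasion. Compare the groups there with adjustment for the D0 pre-treatment value, which is already collected, and require both WS and SPPB to be significant at D21. This agrees with the *and* in H1, with the Discussion and with the two-session hypothesis. It holds the error at 5% or less without splitting alpha. State whether the 5% is one-sided or two-sided.

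Alternatively, make WS at D21 the sole primary outcome, which matches the sample-size basis, and state openly that SPPB becomes key secondary.

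Under either option, declare D7 post secondary, and D0 post and D7 pre descriptive with confidence intervals only. Make the choice before any outcome is compared by group. The article reports that the trial had not gone beyond inclusion.

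The cost is a few sentences in the hypothesis, outcome and analysis sections, and the matching registry entry. Immediate effects become supportive only. Requiring both outcomes lowers joint power below the 90% stated for WS: with SPPB power p, it lies between 0.90 + p − 1 and the smaller of 0.90 and p. If p were 0.80, for illustration, that is 70–80%. The documents give no value for p, and the ceiling effect they note for SPPB may make it low. Keeping all eight tests with Bonferroni would be dearer: at 0.05/8 = 0.00625 one-sided, 29 evaluable or 33 per group, or 64% power for WS with 18 evaluable.

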As a 4th step, the practitioner will perform a “myofascial release technique of the cervical aponeuroses” [50–55]. For the pre-vertebral deep cervical aponeurosis, one hand is placed at cephalic level at the base of the occiput exerting cephalic traction, the other hand is placed at the level of the posterior surface of Thoracic 4 (T4) and exerts anterior pressure and caudal traction—Fig. 2d. For the middle cervical aponeurosis, one hand is placed on the lower part of the mandible and exerts cephalic traction and the other at the level of the sternal manubrium and exerts caudal traction—Fig. 2e. Swallowing is required on exhalation. For the superficial cervical aponeurosis, the hands will be placed successively: at the level of the upper occipital curved line and on the right, then the left scapular spine; then at the level of the lower edge of the mandible and the upper edge of the homolateral clavicle, on one side then on the other—Fig. 2f, g. The 2 hands exert opposing pulls. Each stretch is done over 15 breathing cycles.

For the placebo group, the patient will receive a so-called "light touch" treatment which consists of applying light pressure with broad support from both hands on either side of the joint, in contact with the skin, without equal bone pressure or therapeutic intention, for a duration comparable to interventional group. Thus, the positions of the placebo treatment will be the same as previously described for the group treated with MFR so that the credibility of the placebo treatment is acceptable, with the difference of less manual pressure applied: only in contact with the skin.

## Outcomes

### Primary outcome

The primary outcome of this study will be WS and the SPPB test score.

### Secondary outcome

The secondary outcomes will be as follows: HRV, cervical range of motion, cervical muscle strength, quadriceps strength, static posturography and plantar support.

### Data collection

All data except HRV and posturographic data will be collected and noted by the evaluators on paper records specific to the evaluation. HRV, posturographic and plantar data will be collected and automatically stored in individual file folders (secure by password) in a computer belonging to University Claude Bernard Lyon 1 (UCBL1) used exclusively for the study and protected by password too. After the conclusion of the data collection, the data will be transcribed in an Excel® spreadsheet by an examiner using codes to preserve volunteer identification. All data will be saved on an encrypted UCBL1 server. Synchronization between the computer and the server will be ensured by the software Druva inSync ®.

### Method for data collection

The timing of the measurement session is illustrated in Fig. 1 and their progress is described point by point below.

#### Baseline measures

On the day of inclusion, a questionnaire will be given to each participant to obtain demographic information, note any previous related injury, establish a physical activity profile and question the presence of balance disorders. If any related pain is reported, it will be evaluated on a numerical scale ranging from 0 (no pain) to 10 (worst pain).

Participant weight and height as well as blood pressure will be collected on D0, 7 and 21. Patients will be questioned on any adverse events and pain will be evaluated if necessary.

#### Questionnaire

An SF-36 questionnaire [56] will be distributed before first intervention for self-completion to assess health-related quality of life, allow to characterize the population and possibly to better understand atypical responses to treatment.

#### HRV

Participants will be equipped with a heart rate monitor (Polar RS800) and a heart belt to collect HRV. The watch will be placed on the subjects' wrists and the belt on the chest (under the pectoral muscles for men and under the bra for women). The skin under the sensor will be slightly moistened to ensure good electrical contact and to avoid artifacts. The belt must be tight enough to ensure that the sensor is in perfect contact with the skin but must remain comfortable. Regarding the Coronary Flow Variation (CFV) measurement protocol, a recent study demonstrated that a new Smartphone algorithm, based on R-R interval stabilization analysis, allows CFV measurement in only 5 min, providing results similar to the conventional methodology in the setting of a falls clinic [57]. Thus, a total recording time of 5 min, in the supine position and with spontaneous breathing, will be performed on each patient. Analysis of the HRV data will be performed using Kubios HRV software.

#### Cervical range of motion

Secondly, the patients will be seated in a neutral position, with their backs against the back of the chair, and will perform the cervical range of motion tests. For this, the experimenter will use a measuring tape and the anatomical points previously identified: ear tragus, chin symphysis, anterior angle of the acromion, sternal incisure. The subject will be asked to perform movements of flexion, extension, right rotation, left rotation, right tilt, and left tilt, returning to the neutral position each time. All movements will be performed 3 times. The measurement will retain the difference between the neutral position and the maximum position of the movement [58].

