If the management of the cervical spine seems to be of interest in balance strategy, its vascular and neurological environment makes investigation and local treatment delicate especially in elderly. Myofascial Release (MFR), which is a form of manual therapy, seems particularly appropriate as it is non-invasive and can be adjusted to the recommendations of use. MFR needs application of a low load, long duration stretch to the myofascial complex, intended to restore optimal length, decrease pain, module neural transmission and improve function. The effects of neuromuscular stimulation of the cervical region remain poorly explored. Studies have shown that the application of vibrations to the cervical spine improves sensorimotor function and decreases postural sway in subjects with neck pain, while it alters head positioning in healthy subjects [32, 33]. Applied on C4 level this technique could provide stimulation of the carotid sinus and its baroreceptors, the superior cervical ganglion, the nuchal ligament, the longus neck muscle and the vestibulospinal reflex. An other technique commonly applied in MFR, usually called “suboccipital decompression”, seems to have an interesting impact on different postural determinants, in particular the cranio-cervical angle, the position of the head or even the stiffness of the posterior chains of the lower limbs [34, 35]. This technique enables an action on the oculo-cephalogyre muscles (the rectus capitis posterior major and minor, obliquus capitis superior and inferior) and the vestibulospinal reflex as well as the upper cervical proprioceptors, the neurovegetative structures of the posterior torn hole (X and XI) and of the carotid corpuscle by anastomosis. Other manual protocols aimed at the myofascial system as a whole or more specifically in the neck region have been evaluated and seem to indicate a favourable effect on balance, especially on anteroposterior sway [36] which is a parameter characterizing the displacement of the CoP, cervical mobility [37, 38] or even the Time Up and Go Test (TUGT). Unfortunately, these studies are sometimes of questionable methodological quality whether this is because of a small number of subjects, the absence of a controlled or placebo group or even a timing of different treatments depending on the groups.

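### Cervical mobility is scored from a neutral head position that the treatment may itself shift, so a change of posture could be recorded as a change in flexion and extension range

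*Protocol article*

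**What the plan says.** The Cervical range of motion section starts from a seated posture: "the patients will be seated in a neutral position, with their backs against the back of the chair". It names no head or gaze reference, though it cites a published method. Distances are taken by tape: "the experimenter will use a measuring tape and the anatomical points previously identified", the points being the tragus, chin, acromion and sternal notch. The participant makes "movements of flexion, extension, right rotation, left rotation, right tilt, and left tilt, returning to the neutral position each time", and the value kept is defined as follows: "The measurement will retain the difference between the neutral position and the maximum position of the movement". No full arc is named.

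The Background says that suboccipital decompression "seems to have an interesting impact on different postural determinants, in particular the cranio-cervical angle, the position of the head". The Intervention section makes this the first technique in the treated group. Sham uses the same hand placements with skin contact only. The measurements are repeated after treatment on D0 and D7, and made once on D21.

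Cervical mobility is a secondary objective; the secondary aims are listed as "including cervical strength and mobility as well as lower limb strength, ground support and HRV". The same data may be used to explore relationships between parameters. The statistical section calculates Cohen's d for all outcomes, with thresholds of 0.20, 0.50 and 0.80.

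**The concern.** A half-range counted from neutral mixes two quantities: how far the neck can go, and where the head rests before it moves. The protocol's own rationale raises the possibility that the active treatment changes the second. If it does, the zero point moves in one arm and not, or less, in the other.

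Randomisation balances posture before treatment, not a shift that follows treatment. Blinding the evaluator does not help either, because the shift would be real and correctly measured. The error would lie in calling it mobility.

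At stake is the reading of one secondary outcome, and of any association between cervical mobility and balance that is explored with it. The distinction bears on the trial's explanatory aim, since head posture and neck mobility are different routes by which the neck might influence balance.

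**Working it through.** **The plan's own figure.** There is none for this outcome: the article gives no SD and no expected change for cervical range of motion. Its sample size of 20 per group is for walking speed and does not enter here.

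**Flexion and extension.** Assume that both are read on one landmark pair, such as chin to sternal notch. Let N be the neutral distance, F the end-flexion distance and E the end-extension distance. Under the stated definition:

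- flexion = N − F
- extension = E − N
- sum = (N − F) + (E − N) = E − F

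If N becomes N + x while F and E stay put, flexion changes by +x, extension by −x, and the sum does not change. With assumed distances F = 2 cm, E = 19 cm and N = 12 cm:

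| Shift x (cm) | Flexion (cm) | Extension (cm) | Arc E − F (cm) |
|---|---|---|---|
| 0 | 10 | 7 | 17 |
| 0.5 | 10.5 | 6.5 | 17 |
| 1 | 11 | 6 | 17 |
| 2 | 12 | 5 | 17 |

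The pattern follows from the definition; only the distances are invented.

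**Rotation.** Here the acromion is a paired landmark, and I assume that each side is read to its own acromion. In an assumed geometry the chin lies on the midline, 10 cm forward of and 6 cm above the line joining the two acromions. Each acromion is 18 cm to the side, and end rotation is 60°.

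- Baseline neutral distance: √(18² + 10² + 6²) = 21.448 cm. End-range distance: 12.175 cm. Each rotation = 21.448 − 12.175 = 9.273 cm.
- Neutral moved 2 cm backward, end positions unchanged: neutral distance √(18² + 8² + 6²) = 20.591 cm. Each rotation = 20.591 − 12.175 = 8.416 cm. Both sides fall, and the right-plus-left sum goes from 2 × 9.27 = 18.54 to 2 × 8.42 = 16.84 cm.
- Neutral turned 5° to the right instead: right rotation 8.53 cm, left rotation 9.99 cm, so the two sides move in opposite directions.

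A forward or backward shift therefore moves both rotations the same way and does not cancel when the sides are added. The same reasoning applies to tilt if each tragus is read to its own acromion. In both cases the end-range distance (12.175 cm here) does not contain the neutral reading at all.

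**Size on the scale the plan will use.** Spurious d = shift / SD, with both assumed:

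| | SD 1.0 cm | SD 2.0 cm |
|---|---|---|
| Shift 0.3 cm | 0.30 | 0.15 |
| Shift 0.5 cm | 0.50 | 0.25 |

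In flexion and extension the two signs would be opposite. Against the article's thresholds, these values run from below small to medium.

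**The case against.** The strongest reply is that the shift is only a possibility. The Background reports the postural effect in hedged terms, from cited work. No head-posture outcome is listed, and no shift of neutral is predicted for this trial. The back is supported, and the cited measurement method, which is not at hand, may standardise the head. A condensed article can leave that detail elsewhere. The end positions might also move along with the neutral. All of this stands, and it makes the point conditional.

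It may also be said that arcs are a derived-variable choice for an analysis plan, that a mirror pattern in flexion and extension would be visible to anyone who looks at both, and that the primary outcomes are untouched. The last is correct. On the first, the article does not leave the variable open: it defines it as maximum minus neutral. On the second, a visible mirror pattern would raise suspicion, but half-range differences alone could not show how much was posture.

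A reader might infer three stronger things that the document does not support:

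- That a false gain and a false loss will occur. This needs a shift in neutral, which the document only suggests is possible.
- That all six movements would show a gain on one side and a loss on the other. For rotation and tilt, that needs a neutral that turns or tilts. The head-position effects described in the Background do not predict this.
- That adding right and left removes neutral in every plane. On paired landmarks it does not, as the rotation example shows.

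**Conclusion.** The point holds in conditional form. The retained variable depends on resting head position; the article fixes that position only by back support; and its own Background suggests that a technique applied with therapeutic pressure in one arm alone may alter it. If neutral shifts and the end positions do not, flexion and extension change by equal and opposite amounts without any change in mobility. That result is exact when both are read on the same landmarks. Rotation and tilt may also be distorted, in a direction that depends on how the head moves.

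The size is unknown. The d values of 0.15 to 0.50 are assumed shifts divided by assumed SDs and show scale only. Walking speed, the SPPB score and the sample size are unaffected. The change is worth making before the data are analysed because it is cheap and separates two quantities that the trial wants to tell apart.

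**What to change.** 1. Analyse sagittal mobility as the flexion-to-extension arc: end-extension distance minus end-flexion distance, on the same landmarks.
2. For rotation and tilt, analyse the end-range distances to the fixed landmark on each side, not summed half-ranges.
3. Report the neutral distances separately as a posture variable, so that a shift, if there is one, is seen as such.
4. Keep the single-direction half-ranges as descriptive.
5. State the head reference that defines neutral. If the cited method already sets one, a sentence saying so is enough.

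No new measurement is needed, because each half-range already requires a neutral and a maximum reading. Both readings should be entered on the record, not only their difference; the wording on what is retained leaves this unclear. The cost is a few more derived variables.
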